### Outcomes

The study will conduct evaluations at five time points, all scheduled to coincide with the onset of the first day of the menstrual cycle. The initial evaluation (baseline) will be conducted before any interventions occur, specifically on the first day of the participant’s first menstrual cycle. The second evaluation will occur after the completion of all 20 intervention sessions, specifically scheduled for the first day of the participant’s third menstrual cycle. Follow-up assessments will be conducted monthly, specifically on the first day of the participant’s third through fifth menstrual cycles. Figure 1 illustrates the evaluation process. The initial evaluation will include anamnesis, physical examination, pain assessment, and questionnaires.

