### Sample size

The sample size will follow previous research conducted by our group. The numerical rating scale for pain is the primary outcome of assessing women affected by chronic pelvic pain. The participants also attended five sessions of tDCS using a C3/Fp2 assembly.^19^ G*Power (V. 3.1.9.4, Düsseldorf, Germany) estimated the power and sample size requirements through the use of the F-test from a repeated measures analysis of variance, including the main effects of group and time and the two-way interaction between group and time. Based on an alpha of 0.05 and power of 0.80, two groups (active group and sham group), sphericity of 1 and effect size of 0.25, a total of 34 participants will be required, with 17 participants randomised to each group. With anticipated attrition, we will add six more participants, totalling 40 participants (active group, n=20; sham group, n=20).

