### Randomisation, allocation concealment and blinding

A numerical sequence generated by appropriate software will assign each participant to the active tDCS group or the sham tDCS group, using a 1:1 allocation ratio. Each participant will be equally likely to belong to any group. An independent researcher not involved in the assessment or intervention will conduct all processes. Allocation concealment will be performed using opaque envelopes. Volunteers and researchers involved in assessments and interventions will maintain blinding to the participants’ allocation throughout the study.

Additionally, all procedures regarding the use of home-based self-administered tDCS will be performed for the sham group. First, the participants will position the device and turn it on. Then, they must follow the instructions and use the smartphone application. However, the tDCS will administer 2 mA of current with a ramp-up and ramp-down period of 30 s. Sham tDCS will involve administering active stimulation for a brief duration to replicate sensations (itching and tingling) observed during active tDCS.^21^

To initiate the tDCS protocol, participants will receive a code via email to access the smartphone application, allowing them to unlock 20 sessions of tDCS (one per day). The allocation of active or sham stimulation will be known only to a single researcher not involved in assessments or intervention.

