### Statistical analysis

SPSS software version 21.0 (IBM Corp., Armonk, NY, USA) will analyse the data. We will describe the clinical sociodemographic characteristics using mean and SD for continuous variables and frequency and percentage for dichotomous variables. Independent t-test and X^2^ will analyse continuous and categoric sociodemographic data, respectively. Intention-to-treat analysis will include the data from participants who do not complete the entire treatment protocol. We will define the significance level in all statistical testing as a p value less than 0.05. After data collection, we will identify the best distribution to represent the data according to the residuals Q–Q plot and histogram. The generalised estimated equations or mixed model will analyse the data (primary and secondary outcomes at baseline, after the fifth session, after the last session and follow-ups). We will also evaluate if it is necessary to insert fixed or random factors into the constant based on A/C, B/C and Q/C indices, X^2^/DF and the intraclass correlation coefficient. The link function will estimate the results according to the distribution of the dependent variable. Time, group (active and sham groups) and the interaction between them will represent the independent factors. The mean, mean difference, SD, 95% CI and p value for baseline, after the last session and follow-ups will illustrate the results. Cohen’ d will represent the effect size.

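### Baseline pain is modelled as one more visit with arm means left free and no prespecified baseline adjustment, so the analysis is unbiased but less precise than the data allow

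*Protocol article*

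**What the plan says.** The Statistical analysis section plans generalised estimating equations or a mixed model for primary and secondary outcomes, and it lists baseline among the analysed time points. The fixed part is given in one sentence: "Time, group (active and sham groups) and the interaction between them will represent the independent factors". The section names neither a baseline covariate nor a common baseline mean. It does leave room to insert fixed or random factors, judged on fit indices once the data are in, but does not say that baseline pain would be one of them. It promises means, mean differences and confidence intervals for baseline, the end of treatment and follow-up, without saying which contrast is the treatment effect.

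The Sample size section uses the same structure, a repeated-measures analysis of variance "including the main effects of group and time and the two-way interaction between group and time". Its inputs are "Based on an alpha of 0.05 and power of 0.80, two groups (active group and sham group), sphericity of 1 and effect size of 0.25", and it concludes that "a total of 34 participants will be required, with 17 participants randomised to each group". Six more are added for attrition, giving 20 per arm.

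Two further statements matter. Under Outcomes, "The initial evaluation (baseline) will be conducted before any interventions occur". Under Randomisation, participants are allocated "using a 1:1 allocation ratio".

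**The concern.** Baseline is measured before treatment in randomised arms, so any T0 difference between arms is chance. A model with time, group and their interaction, and T0 as a level of time, estimates that difference freely. The group-by-time contrast at a later visit is then a difference in raw change scores, which carries the full noise of the T0 measurement. If the raw difference at a visit is read off instead, the T0 value is not used at all. Neither makes efficient use of a measurement already planned for every woman.

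The group main effect has a further weakness: it averages over all levels of time, including T0, where no treatment effect can exist.

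With 17 to 20 women per arm, precision is scarce, and this gain needs no extra participants, visits or measurements.

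**Working it through.** **Inputs from the protocol article.** Alpha 0.05, power 0.80, two groups, "sphericity of 1 and effect size of 0.25", 34 women before attrition and 40 after (Sample size); five assessments, T0 to T4 (Participant timeline). **Not given:** the number of measurements *m* used for sizing, and the correlation *rho* between baseline and later values. Both are assumptions below.

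**Step 1: reproduce the plan's figure.** For the within-between interaction, lambda = f²·N·m/(1 − rho), df1 = (k − 1)(m − 1), df2 = (N − k)(m − 1). With k = 2, m = 2, rho = 0.5, f = 0.25 and N = 34:

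lambda = 0.0625 × 34 × 2 / 0.5 = 8.5, df = 1 and 32, power 0.807.

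N = 32 gives 0.781, so 34 is reproduced. This does not establish rho = 0.5 as the plan's value, because other combinations also give 34 (for example, the between-group test with m = 4 and rho = 0). With m = 5 and rho = 0.5 the interaction formula gives 22.

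**Step 2: put f on the scale of a group difference.** For two groups and two times, the difference in change is 4f SD = 4 × 0.25 = 1.0 SD. The power figures below use this difference.

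**Step 3: variances at one post-baseline visit** (per SD², equal SDs, same arm sizes):

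- group-by-time contrast with free T0 means: 2(1 − rho)
- raw group difference at the visit: 1
- baseline-adjusted difference: 1 − rho²

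The adjusted variance relative to the interaction contrast is (1 − rho²)/(2(1 − rho)) = (1 + rho)/2. Relative to the raw difference it is 1 − rho².

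| rho | saving against group-by-time contrast | saving against raw visit difference |
|---|---|---|
| 0.3 | 35% | 9% |
| 0.5 | 25% | 25% |
| 0.7 | 15% | 49% |
| 0.8 | 10% | 64% |

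An information-matrix calculation with five visits and compound symmetry compared free T0 means with a common T0 mean. It gave variance ratios of 0.65, 0.75 and 0.85 at rho 0.3, 0.5 and 0.7, equal to (1 + rho)/2.

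**Step 4: power for a 1.0 SD difference** (noncentral t; one degree of freedom deducted for the covariate at a single visit):

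| per arm | rho | group-by-time contrast | raw visit difference | baseline-adjusted |
|---|---|---|---|---|
| 17 | 0.3 | 0.666 | 0.807 | 0.841 |
| 17 | 0.5 | 0.807 | 0.807 | 0.903 |
| 17 | 0.7 | 0.954 | 0.807 | 0.977 |
| 20 | 0.3 | 0.740 | 0.869 | 0.898 |
| 20 | 0.5 | 0.869 | 0.869 | 0.945 |
| 20 | 0.7 | 0.978 | 0.869 | 0.991 |

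Below rho 0.5 the change-score contrast does worse than ignoring baseline, because 2(1 − rho) then exceeds 1. At rho 0.5, the total for 80% power falls from 34 to 26 with adjustment.

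The adjusted figures are slightly optimistic, because estimating the slope costs a factor of about 1 + 1/(N − 4). At N = 34 and rho 0.5 the ratio becomes 0.75 × (1 + 1/30) = 0.775, a saving of about 23% instead of 25%.

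**Step 5: the group main effect.** With a constant effect D at T1 to T4 and none at T0, the equally weighted average over five visits is (0 + 4D)/5 = 0.8D.

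**The case against.** The best defence is that nothing here is an error. The model is unbiased under randomisation and has the same structure as the sizing model. On the inputs that reproduce 34, it reaches power 0.807 at 34 and 0.869 at 40. A reader might infer that the trial is underpowered or its analysis invalid; the documents support neither.

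Several other stronger readings also fail:

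- **That the model is closed to other terms.** The article lets factors be inserted later. That does not fill the gap, since the choice is made after data collection on fit indices and baseline is not named.
- **That having baseline in the response is the fault.** It is a legitimate choice and keeps women with incomplete visits, which suits the intention-to-treat aim. The loss against adjustment arises because the arm means are left free at T0.
- **That a quarter of the variance is lost.** This holds only at rho 0.5 for a single visit, and the article gives no rho.
- **That the gain is largest here because entry requires pain of at least 4.** No contrast is named, and the two candidates move in opposite directions: low rho gives the largest saving against change scores and the smallest against raw visit differences. Screening also uses a numeric rating scale while the outcome is a VAS, and no spread is given for either.

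The condensed format and an unseen analysis plan could excuse a missing covariate list. They do not remove the point: the article states the fixed structure, and that structure uses baseline inefficiently under either reading of the contrast.

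**Conclusion.** The point holds as a loss of efficiency and should be corrected before analysis. It is not a validity problem. For any rho strictly between 0 and 1, baseline adjustment has smaller large-sample variance than both contrasts the article could mean. The size depends on rho and on the contrast: a saving of 10% to 35% for rho from 0.8 down to 0.3 if the effect is the group-by-time contrast at one visit, and 9% to 49% for rho from 0.3 to 0.7 if it is the raw difference at a visit. At rho 0.5 both give 25%.

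These figures assume a continuous outcome, a linear model and equal SDs at both visits. They are not shown for other distributions or links, which the article allows.

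Separately, the group main effect is a poor summary of treatment, because it includes a visit at which the effect is zero by design.

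**What to change.** For VAS and other continuous outcomes with a T0 value, add one sentence that fixes one of these before the data are analysed:

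1. Keep T0 in the response and constrain the arm means to be equal at T0, with group differences only at T1 to T4. This keeps women with incomplete visits and needs no extra parameters.
2. Use T1 to T4 as the response, with the T0 value and T0-by-time as covariates. This adds four parameters: one main effect and three interaction terms.

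In either case, report the adjusted group difference at each post-baseline visit, with its confidence interval, as the treatment effect in place of the group main effect. State that baseline handling is prespecified and does not depend on the later choice of factors by fit indices.

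The cost is the added sentence and, under the second option, a few parameters. No change to recruitment, visits or measurements is needed.

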### Harms

The researchers will carefully monitor adverse events in all steps of the study by asking patients, after each session of stimulation and during the follow-up periods, if they experienced any adverse events and the relationship of these events to treatment with tDCS. Any adverse event during the research period will be registered and considered for data analysis. The researchers will interrupt the sessions if any risk to the patients is suspected. To evaluate adverse effects, we will record any musculoskeletal symptoms, such as itching, tingling, burning sensation, headache, nausea and dizziness. Withdrawals will be excluded from the protocol and integrated as intention-to-treat analysis. Adherence to the number of missed sessions, number of dropouts and possible adverse events reported will be assessed.

### Ethics and dissemination

The Department of Physical Therapy of the Federal University of Rio Grande do Norte is the place where the researchers will collect the data. The study will follow the principles of the Declaration of Helsinki and Resolution 466/12 of the National Health Council. The researchers registered the protocol in the Brazilian Clinical Trials Registry (n° RBR-747k8vb) and obtained approval from the Federal University of Rio Grande do Norte Ethics Committee (n° 6.037.756).

Participants will retain the freedom to decline participation or withdraw their consent at any point during the study, without incurring any penalty or impact on their care. Should any issues arise during the trial, participants will have the right to receive free assistance from the designated responsible researcher. This study will not involve participants at risk of death or interventions that are harmful. Therefore, it will not be necessary to create a data safety monitoring board. All procedures will adhere strictly to international ethical and scientific standards, following the guidelines outlined in Good Clinical Practices for research involving human participants. The study findings will be communicated to participants through a public symposium and on social media.

The literature indicates that serious adverse events directly linked to tDCS are rare. All adverse events will be promptly reported to the principal investigator. Serious adverse events will be recorded and analysed by the study principal investigator and, if necessary, submitted for review by the Ethics Committee. No auditing procedures are planned; however, if required, any amendments to the research protocol will be submitted to the Ethics Committee for approval. On completion of the study, the datasets used will be made available to interested parties on reasonable request to the corresponding author.

### Patient and public involvement

All participants will be briefed on the trial’s objectives and procedures, emphasising voluntary participation. The researchers will inform the participants about the research procedures and will obtain a written Informed Consent Form signed by the participants before initiating the study. Following the study, all participants who received the sham tDCS stimulation will be invited to undergo the active tDCS. The principal investigator will store the data for 5 years in the Physiotherapy Department at the Federal University of Rio Grande do Norte. After this time, he will incinerate all the documents. This study will not share any personal information related to participation in the research during or after the study. The results of the study will be communicated to participants through a popular symposium.

## Discussion

This study protocol represents the pioneering use of a home-based self-administered tDCS approach for women suffering from primary dysmenorrhoea. The investigation will entail a comprehensive analysis of long-term treatment outcomes involving 20 consecutive sessions and a 3 month follow-up period. Primary dysmenorrhoea is recognised as a chronic pain condition that profoundly impacts women worldwide during their reproductive years.^5^ Moreover, individuals affected by primary dysmenorrhoea often present comorbid symptoms of depression, anxiety and affective disorders.^36^

During the COVID-19 pandemic, there has been a significant number of studies employing home-based self-administered tDCS or remote tDCS.^37^ This innovative approach is designed to enhance patient adherence, reduce costs and evaluate the effectiveness of remote neuromodulation treatments.^37^ Promising results have been demonstrated for remote tDCS treatment across different conditions. The introduction of new devices that show excellent usability, safety features, ease of use and interactive interfaces could greatly benefit a substantial number of patients, particularly those with significant impairments or facing transportation challenges.

The intermittent nature of pain experienced by women suffering from primary dysmenorrhoea, particularly exacerbated in the days leading up to and during menstruation, leads to brain reorganisation and central sensitisation.^5^ Neuroimaging studies have elucidated significant associations between pain and morphology as well as dynamic functional alterations in various brain regions implicated in the cognitive and affective regulation of pain.^5 6^ tDCS emerges as a neuromodulation technique aiming to improve pain in several chronic pain conditions. For tDCS, the most used target to modulate pain is the M1.^9^ Anodal stimulation on M1 increases the activity of this brain area and modulates the neural network by cortico-thalamic pathway.^38^

Other brain areas typically involved in the pain regulatory system also seem to be modulated, such as grey periaqueductal substance, cingulate cortex, indirectly the amygdala, primary and secondary S1.^38^ Prefrontal cortex is a second target usually studied for treating chronic pain.^38^ This is an executive area with a direct association with pain-related emotions, probably involved in the affective-emotional networks related to pain.^19 38^ Studies suggest that the DLPFC upregulates positive reactions to positive emotional stimuli and down-regulates negative reactions to emotional stimuli.^38^ This is important because women suffering from primary dysmenorrhoea show not only pain disturbance but also mood disorders including emotional distress, depression and anxiety.^1 7^ Physical symptoms are usually described and include low physical function or incapacitation before and during the menstrual period.^1 2^

This study protocol of home-based self-administered tDCS study aims to improve women’s health by assessing physical function, mood and electrophysiological aspects. The population proposal will involve only women affected by primary dysmenorrhoea. However, future studies could investigate other chronic pain conditions associated with women’s health that include interstitial cystitis, endometriosis and fibromyalgia.
